#### Aim 2: patient reported outcomes

Secondary outcomes will aim to evaluate improvement in patients reported outcomes, and use of other substances. Patients’ quality of life (measured by EQ5D-5L), anxiety disorders (GAD-7), quality of sleep (ISI), time to first hospitalization after inclusion (SNDS), occurrence of falls, dependence on BZDR (ECAB), autonomy (IADL) and use of other substances will be assessed.

A stratified analysis by type of BZDR (hypnotic or anxiolytic) will be carried out on each of the outcomes to determine the impact of the indication on the implementation elements.

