#### Step 2: medication treatment dispensing and MI

Following the medical consultation, the patients will go to the pharmacy to get their medication treatment dispensed. They will be given a kit of patient education materials addressing the risks of BZDs and the benefits of reducing/stopping their use. This kit will be designed on the basis of patient education materials produced by the Canadian Deprescribing Society^1^ and adapted to the French context. The pharmacist will then plan with the patients 3 MIs to be carried out within the next 3 months. These interviews will last 30 to 60 min and will address the risks of using BZDR, as well as the benefits and modalities of stopping them. MI is a client-centered, semi-directive method for enhancing intrinsic motivation to change by exploring and resolving ambivalence (22). It is intended to work through four main principles: express empathy, support self-efficacy, roll with resistance, and develop discrepancy. During these interviews, the pharmacist will provide information about non-pharmacological ways to improve sleep or reduce anxiety, prevention of rebound phenomena, and will provide an example of de-escalation of doses (i.e., progressive reduction). The pharmacist will identify the patients’ representations of their medication and pathology (insomnia, anxiety), and will understand the barriers and facilitators for deprescribing. Any question the patients may have will be addressed. The choice to stop or reduce the dose of the BZDR will be the result of a shared medical decision (trio patient – GP – PC). To facilitate implementation, the pharmacists of the intervention arm will receive a 2-day specifically designed training course in MI by a certified organization prior to the intervention (Table 2). They will be given guidelines on the risks associated with BZDR, their deprescribing, and the management of patients who were deprescribed. If required, the pharmacists will be supported by the interventional public health department of the promoting center which will accompany them in their first MI. To avoid contamination, pharmacists working in pharmacies randomized in the control group will not be trained in MI and in deprescribing until after the study is completed.

**Table 2 tab2:** Objectives and program of the pharmacist’s training course in Motivational Interview.

Pedagogical objectives	

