### Data sources and collection

The implementation outcomes will be measured by different procedures detailed below (see Outcomes section).

The sociological study will consider the variability of practice locations to be more representative: rural, urban, peri-urban. Depending on the location of the practice, the patient may have different social characteristics that will probably require professionals to adapt (vocabulary, arguments, conduct of the interview, etc.). Four days of observations will be conducted with pharmacists who have just been trained in MI to study, in action, how they conduct their first interviews with the older adults. These same pharmacists will be observed a second time at the end of the study, to see how their approach to MI has evolved.

A first wave of ten semi-structured interviews will be conducted with older adults who have already been seen by their pharmacist, to see what effects the pharmacist has had on their representations of BZDR and on their consumption.

Finally, three focus groups will be carried out, one with CPs, one with GPs and one with pairs. The first two will allow to identify any difficulties experienced in this interprofessional collaboration, but also what has been facilitated. The last focus group will allow the pairs to exchange and compare their point of view on multidisciplinary work and relevance of the collaboration.

Regarding the effectiveness of the intervention, the consumption of reimbursed drugs and the co-payments of the system will be assessed using the National Health Data System (SNDS) (23). This database provides access to all reimbursed healthcare, including drugs dispensed in pharmacies.

The outcomes concerning the clinical evolution of the patients will be measured using questionnaires administered to the patients by telephone by a clinical research associate.

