##### Cost-utility

Economic efficiency of the implementation effort will be assessed following the HAS 2020 recommendations (25). A Cost-Utility Analysis (CUA) expressed as a cost per Quality Adjusted Life Year (QALY) will be performed from a collective perspective and with a time horizon of 12 months. The CUA will consider the direct costs of care from randomization to M12. Hospital and city care consumption data related to the management and its consequences will be collected in both arms via the Health Insurance database (SNDS). The data collected will include: medications, medical consultations, hospitalizations if applicable, and emergency room visits. A budgetary impact analysis from the point of view of the Health Insurance will be carried out following the CUA. It will be based on different scenarios of 5-year diffusion levels of the joint intervention.

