### Sample size and power

The calculation of the number of subjects needed is based on the effectiveness outcome, on the basis of the following assumptions: risk α equal to 5%, statistical power equal to 80, 5% deprescribing proportion in control group based on current trend, a proportion of at least 15% in the intervention group, an intraclass correlation coefficient of 0.05 (26) and a number of 20 GP-CP pairs per arm. The number of patients to be recruited will be 400 (200 per arm), based on the inclusion of 10 patients per GP-CP pair, with 20 GC-CP pairs per arm during the 12 months of inclusion (27). To reach target sample size, various networks will be involved in recruitment: primary care research network, professional associations, regional unions of practitioners, university training masters.

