### Limits

Despite these strengths, our trial has several limitations. Firstly, neither the patients nor the GP-CP pairs will be blinded due to the pragmatic design of the trial (52). However, the statisticians and the clinical research officer will be blinded to reduce the risk of confirmation, monitoring and evaluation bias. Secondly, it is likely that the pairs agreeing to participate in the study will be health professionals already convinced by the deprescribing approach, which is why this study is randomized and controlled. In addition, although pharmacists will be trained in MI by a certified organization, some may be more or less comfortable than others and the implementation of the intervention may depend on the operator of the training. This will be measured by the fidelity of the study to the protocol. Finally, a limitation of this study is that the evaluation of a multifaceted intervention prevents the determination of the specific component(s) responsible for the observed outcomes or failures at the conclusion of the study.

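### Falls appear to rest on telephone self-report by unblinded patients, only one arm of whom is taught BZDR risks; SNDS events already collected could serve as an objective supporting check

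*Protocol article*

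**What the plan says.** The Background names falls and fractures among the consequences of BZDR and names falls again as a risk in older adults. Under Aim 2: patient reported outcomes, the secondary list ends: "occurrence of falls, dependence on BZDR (ECAB), autonomy (IADL) and use of other substances will be assessed". In that sentence only time to first hospitalization carries an SNDS tag. The scales have their instruments named; falls have neither source nor instrument.

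Data sources and collection says that outcomes on patients' clinical evolution come from "questionnaires administered to the patients by telephone by a clinical research associate". In that section the SNDS is assigned to reimbursed drugs and co-payments. The Abstract is broader: it gives databases and questionnaires together as the sources for medication and clinical outcomes, without saying which serves which.

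Under Step 2, intervention patients receive a "kit of patient education materials addressing the risks of BZDs" and three interviews of 30 to 60 minutes that cover those risks. Under Step 3, control patients have usual care. The Limits section says that "neither the patients nor the GP-CP pairs will be blinded", while the statisticians and the clinical research officer will be.

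For the cost-utility analysis, SNDS data are collected in both arms and include "hospitalizations if applicable, and emergency room visits".

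**The concern.** A fall that leads to no care is known only if the patient recalls it and mentions it. Here the patient knows the arm, and in one arm has been repeatedly told about the risks of the drug. The article does not say that the kit or the interviews name falls, but its own Background lists them among the main risks. Patients made alert to the risk may recall more falls, which would look like harm. Patients who have committed to stopping may play falls down, which would look like benefit. A blinded caller does not solve this, because the answer comes from the unblinded patient, and a mixed model cannot separate a difference in reporting from a difference in falls.

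At stake is how one secondary outcome is interpreted. It is a named harm of the drug class, so a reader will look at it.

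**Working it through.** **Inputs from the article (Sample size and power):** "risk α equal to 5%, statistical power equal to 80, 5% deprescribing proportion in control group based on current trend"; at least 15% in the intervention group; intraclass correlation 0.05; 20 pairs per arm with 10 patients each; 400 patients.

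**Inputs not in the documents (assumed, with ranges):** 12-month fall risk p on BZDR, 20 to 40%; relative risk RR of falling on BZDR, 1.3 to 2.0; gap ds between arms in the share of falls reported, 5 to 15 points; share of patients with a fall-coded SNDS event, 2 to 5%.

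**1. The plan's own figure.** Design effect = 1 + (10 − 1) × 0.05 = 1.45. With unpooled variance and a two-sided 5% level, n = (1.960 + 0.842)² × (0.05 × 0.95 + 0.15 × 0.85) / 0.10² = 137.4 per arm, and 137.4 × 1.45 = 199.2. With pooled variance, 141 × 1.45 = 204.45, so 205. The stated 200 per arm reproduces (power at 200 is 79.4%), so the 10-point contrast is a fair planning value.

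**2. True effect against reporting artefact.** Let d be the extra share of patients deprescribed.

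- True effect on fall risk = d × p × (1 − 1/RR)
- Spurious difference = p × ds
- Equal when ds = d × (1 − 1/RR); p cancels

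| RR | 1 − 1/RR | True effect, d = 10 points, p = 30% | Break-even gap, d = 10 points | Break-even gap, d = 30 points |
|---|---|---|---|---|
| 1.3 | 0.231 | 0.7 points | 2.3 points | 6.9 points |
| 1.5 | 0.333 | 1.0 | 3.3 | 10 |
| 2.0 | 0.500 | 1.5 | 5.0 | 15 |
| all falls abolished | 1 | 3.0 | 10 | 30 |

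Across p = 20 to 40% and RR = 1.3 to 2.0, the true effect at d = 10 points is 0.5 to 2.0 points. Reporting gaps of 5, 10 and 15 points at p = 30% create 1.5, 3.0 and 4.5 points; across p = 20 to 40% the range is 1.0 to 6.0 points.

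**3. Precision of the self-reported comparison.** Effective n per arm = 200 / 1.45 = 137.9, if the same intraclass correlation applies to falls. At 30%, SE = √(2 × 0.30 × 0.70 / 137.9) = 5.5 points. The smallest reduction detectable with 80% power is about 12, 14 and 16 points at fall risks of 20, 30 and 40%. A true effect of 1 to 3 points at p = 30% has power of about 4 to 8%.

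**4. What the SNDS measure could show.** Events per arm: 200 × 0.02 = 4 to 200 × 0.05 = 10. True effect at d = 10 points, RR 1.5 to 2.0: 0.10 × 0.02 × 0.333 = 0.07 points to 0.10 × 0.05 × 0.5 = 0.25 points. Power is about 3%, hardly above the 2.5% expected in that direction with no effect.

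**The case against.** **The source is inferred.** A reader might infer that the plan fixes falls as telephone self-report. It does not say so. Another item under the same heading, time to first hospitalization, is SNDS-based; the Abstract mentions databases as well; and the full protocol is not shown. This stands: self-report is the likelier reading, not a stated fact.

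**The size rests on outside figures.** A reader might infer that a reporting artefact would exceed any plausible true effect. The documents give no fall risk, relative risk or reporting gap. The break-even gap rises to 6.9 to 15 points if the contrast is 30 points, the 15% is a stated minimum, and the calculation credits no benefit to dose reductions below 50%. Since the direction of the bias is open, no net bias is shown. This also stands.

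**Little could be declared significant.** With an SE of 5.5 points, an artefact of 1.5 to 4.5 points is 0.3 to 0.8 SE, so a false claim is not likely. That is true, but it also means that an apparent difference would be hard to credit without an outside check.

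**Falls are one secondary outcome, and their modelling can sit in the analysis plan.** Both are right. Their absence from the Statistical analysis section is ordinary condensation and no error, and nothing says that the trial's safety or benefit message will rest on them.

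**Objective data are partly there already.** Hospitalizations are analysed, and falls leading to admission count among them, but as specified these outcomes do not single out falls. The Cost-utility section does not mention coding of cause, so the addition depends on what is coded.

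**Conclusion.** The concern holds as a risk of arm-dependent reporting in one secondary outcome. Unblinded patients, risk teaching in one arm only and the likely telephone source together create it, and a blinded caller does not remove it. At the planned 10-point contrast and an assumed RR of 1.3 to 2.0, a reporting gap of about 2.3 to 5 points would equal the true effect. The direction and actual size of any gap are unknown. The documents do not support saying that the comparison is biased by a given amount, or that SNDS events could replace self-report. The case for change is that an objective check is available at low cost from data already planned for collection in both arms.

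**What to change.** Under Aim 2, state the source of the falls outcome. Add a supporting outcome in both arms from inclusion to M12: hospital stays and emergency visits for a fall or fracture in the SNDS data already collected for the cost-utility analysis, as far as cause is coded. Analyse it in all included patients with account of the cluster effect, and report it with a confidence interval. Keep self-reported falls, and say that no conclusion on falls will be drawn from the telephone data alone.

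The cost is a code list and one further analysis; the sample size does not change. The downside is that only falls leading to care are captured, so the few events cannot serve as a confirmatory test.

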### Study population and recruitment

#### Patients

In order to minimize the risk of subjective pre-selection of patients by the GP, a predefined list of eligible patients per cluster will be sent out to each GP by the Health Insurance according to the inclusion criteria detailed below, before randomization of the clusters and on the basis of the GP’s request. The study population will consist of patients aged 65 years and older, monthly users of at least one anxiolytic or hypnotic BZDR for more than 3 consecutive months (ATC classes N05BA, N05CD and N05CF). Patients meeting the eligibility criteria will be recruited by GPs during their medical encounters.

The inclusion criteria will be: outpatients aged 65 and over, followed by the GP and being delivered their medications by the pharmacist of the GP-CP pair, having a prescription for an anxiolytic or hypnotic BZDR prescribed at least 4 times in the past year, the last prescription being dispensed in less than 3 months and having been dispensed monthly during the last 3 months, affiliated to a social security scheme, and having given consent to participate in the research.

Non-inclusion criteria will be: patients living in an institution, participating in another clinical trial, with any medical condition that contraindicates BZDR discontinuation on the physician’s opinion, unable to participate in an interview or answer a questionnaire and with insufficient autonomy to carry out the steps inherent in the study. Patients living in an institution will be excluded because an unknown part of them have their BZDR not traced in the SNDS database (for administrative reasons), which could induce bias in our study.

If eligible, the patient will be offered to enroll in the study during a standard medical consultation. If he agrees to participate, signed informed consent will then be obtained, and the patient will be assigned a patient number automatically upon inclusion.

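### For outcomes measured in both arms, separate hypnotic and anxiolytic analyses do not test whether the effect differs by type, and no between-type comparison is named

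*Protocol article*

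**What the plan says.** The last paragraph of the article's section Aim 2: patient reported outcomes states: "A stratified analysis by type of BZDR (hypnotic or anxiolytic) will be carried out on each of the outcomes to determine the impact". Read to its end, the sentence gives the scope and purpose as "on each of the outcomes to determine the impact of the indication on the implementation elements".

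The Statistical analysis section describes a mixed logistic model for the effectiveness endpoint and mixed models for the EQ-5D-5L, GAD-7, ISI, ECAB and IADL scores. All compare the two arms. The minimum covariates are age, sex, past attempts and suspected addiction. Neither BZDR type nor an arm-by-type term is named, and no other comparison between the strata is described. Randomisation is not stratified (Randomization section).

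The Patients section admits "monthly users of at least one anxiolytic or hypnotic BZDR for more than 3 consecutive months". A patient who takes both types is therefore eligible, although the stratified analysis lists only two categories.

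**The concern.** The sentence pairs a method with a purpose that the method does not serve. Analysing each type separately gives an effect estimate for each. Whether the indication changes the effect depends on the difference between those estimates and its uncertainty, and neither is produced.

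The danger lies in how two separate results tend to be read. Each stratum is smaller than the trial and has well under 80% power. One significant and one non-significant stratum is therefore a common result even when the intervention works equally well in both. The abstract hopes the results will feed guidelines on the role of community pharmacists, or even legislation, so a spurious contrast between hypnotic and anxiolytic users could influence who is offered the service.

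There is a side issue with the categories. Users of both types have no evident place in a two-way split, and if they entered both strata, the two results would share patients.

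**Working it through.** **Inputs.** From Sample size and power: for the control arm, "5% deprescribing proportion in control group based on current trend"; for the other arm, the plan assumes "a proportion of at least 15% in the intervention group"; for clustering, it takes "an intraclass correlation coefficient of 0.05". It also sets α of 5%, power of 80%, 10 patients per pair and 20 pairs per arm (200 patients per arm). Assumed, because the article does not give them: a two-sided test; type splits of 50:50, 60:40 and 70:30; strata that do not overlap; each split the same in every cluster.

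**1. The plan's own figure.** Design effect = 1 + (10 − 1) × 0.05 = 1.45. With unpooled variance, n per arm = (1.96 + 0.842)² × (0.05 × 0.95 + 0.15 × 0.85) / 0.10² = 137.4, and 137.4 × 1.45 = 199. With pooled variance under the null, 141 × 1.45 = 204. The stated 200 per arm is reproduced.

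**2. Power in each stratum, same true effect (5% versus 15%) in both.** With m patients of a type per cluster, effective n per arm = 20m / (1 + (m − 1) × 0.05). Power = Φ{[0.10√n − 1.96√(2 × 0.10 × 0.90)] / √0.175}. For 50:50, m = 5, so n = 100 / 1.20 = 83.3 and power = Φ[(0.913 − 0.832) / 0.418] = Φ(0.194) = 0.577.

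**3. Chance that exactly one stratum is significant.** Both strata come from the same clusters, so their estimates are correlated: ρ = 0.05 / √(v₁v₂), with v = (1 + (m − 1) × 0.05) / m. For 50:50, v = 1.20 / 5 = 0.24 and ρ = 0.05 / 0.24 = 0.208. The chance that both are significant comes from the bivariate normal distribution. The chance of exactly one is P₁ + P₂ − 2 × P(both). For 50:50 that is 0.577 + 0.577 − 2 × 0.365 = 0.424.

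| Split | Power, larger / smaller stratum | ρ | Both significant | Exactly one significant | Exactly one, if strata were independent |
|---|---|---|---|---|---|
| 50:50 | 58% / 58% | 0.21 | 37% | 42% | 49% |
| 60:40 | 64% / 50% | 0.20 | 35% | 44% | 50% |
| 70:30 | 69% / 41% | 0.19 | 31% | 48% | 53% |

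The last column ignores the shared clusters, so the column before it is the one to use. In the same setting, an interaction test at the 5% level flags a difference about 5% of the time, by construction.

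**4. What the interaction test could detect.** Take a 10-point effect in one stratum (5% versus 15%) and none in the other (5% versus 5%). Variance of the difference = 0.175v₁/20 + 0.095v₂/20 − 2c, where c = 0.05 × (0.0475 + √(0.1275 × 0.0475)) / 20 = 0.000313. For 50:50 this is 0.00210 + 0.00114 − 0.00063 = 0.00261, so the standard error is 0.0511 and power = Φ(0.10 / 0.0511 − 1.96) = 50%. With the effect in the larger stratum, the 60:40 and 70:30 splits give 51% and 48%. With the effect in the smaller stratum at 70:30, the variance is 0.00321 + 0.00088 − 0.00063 = 0.00346, the standard error 0.0589 and power about 40%. A third category for users of both types would lower these figures further.

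**The case against.** The best defence is that this is one sentence in a condensed article. How strata are compared is often left to the full protocol or analysis plan, and nothing here rules out an interaction term. A reader might infer that the investigators have rejected one, or that they will call the effect different when one stratum reaches significance and the other does not. The documents support neither inference: the missing comparison is silence, and no rule based on stratum p-values is written. The point survives in a narrower form because the article does name a method for a between-type question, and that method alone does not answer it.

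The stated purpose also ends with the implementation elements. Some of these exist only in the intervention arm, such as the number and duration of motivational interviews, appointments with the pharmacist and reports to the GP. No arm-by-type interaction can be fitted there, and comparing the types directly is appropriate. This objection stands and limits the point to two-arm outcomes, which are covered because the analysis is planned on every outcome.

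Two further readings go too far. The discordance figure applies to the effectiveness endpoint only; the article gives no effect sizes for the patient-reported scores, so its recurrence across outcomes is not shown. Nor does it follow that users of both types must be dropped or counted twice. They could be classed by main indication, since Acceptability/adoption lists the indication among the variables studied, or given their own category. What stands is that the two categories named do not say where they go.

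**Conclusion.** The concern holds for outcomes measured in both arms. The stratified analysis does not test the difference it is meant to inform, and no between-stratum comparison is named. On the effectiveness endpoint, identical true effects would leave exactly one stratum significant in about 42% to 48% of trials, so the stratum results could be misread as a difference in effect. These figures rest on a two-sided test, the planned 5% versus 15%, the planned intraclass correlation and the assumed splits with exclusive, evenly spread strata. The actual split is unknown.

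A reader might infer that the trial's main result is at risk. It is not: the overall comparison of arms by mixed logistic model is unaffected. The point concerns one subgroup sentence and deserves correction before the data are analysed.

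**What to change.** For outcomes measured in both arms, replace the separate stratified analyses with one mixed model per outcome on all patients. It should contain arm, BZDR type at inclusion (hypnotic only, anxiolytic only, both) and the arm-by-type interaction, with the cluster effect and covariates already planned. Report the interaction estimate with its confidence interval, and take the type-specific effects from the same model. Label the analysis exploratory and draw no conclusion from comparing stratum p-values.

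For outcomes that exist only in the intervention arm, compare the types directly within that arm.

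The cost is a change of wording. Type can be derived from the SNDS dispensing data already planned, so no new data collection is needed. The drawback is imprecision: power for the interaction is about 50% even if the effect is wholly absent in one type, and lower if the effect is confined to a small stratum. A non-significant interaction must therefore not be reported as evidence that the effect is the same in both types.
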